### Sample size calculation

2.8

The sample size was calculated using G*Power software (version 3.1.9.7) based on the change in the primary outcome measure, the VAS scores. Because few previous trials have directly compared manual therapy combined with core stability exercise versus core stability exercise alone in sedentary individuals with CNLBP, the sample size was estimated using the best available evidence from a randomized trial evaluating exercise-based interventions for chronic non-specific low back pain (38). The expected between-group difference in VAS was set at 1.5 points, with a pooled standard deviation of 2.3, corresponding to Cohen’s *d* = 0.65. This effect size was considered clinically plausible and consistent with a moderate treatment effect in musculoskeletal rehabilitation.

In this study, the type I error probability (α) for a two-tailed test was set at 0.05, and the statistical power (1−β) at 80%. Based on these parameters, a total sample size of 74 participants is required. Accounting for a potential 15% dropout rate, the adjusted sample size per group is 44, resulting in a total planned recruitment of 88 participants.

### Statistical analysis

2.9

Baseline and efficacy analyses will be conducted following the intention-to-treat (ITT) principle. The distribution of continuous variables will be assessed using visual inspection of histograms and Q-Q plots, together with the Shapiro-Wilk test. Homogeneity of variance will be examined using Levene’s test. Normally distributed continuous variables will be presented as mean ± standard deviation and compared using independent-samples *t*-tests, whereas non-normally distributed variables will be presented as median and interquartile range and compared using the Mann-Whitney U test. Categorical variables will be summarized as frequencies and percentages and compared using the chi-square test or Fisher’s exact test when expected cell counts are small.

Linear mixed-effects models (LMMs) will be used to assess efficacy. The model will include group, time, and their interaction as fixed effects, with participants as a random effect, adjusting for baseline values. For linear mixed-effects models, assumptions will be checked using residual and Q-Q plots. If substantial violations are identified, appropriate transformations or robust sensitivity analyses will be considered. The group-by-time interaction term will be used to test for between-group differences in the change from baseline for both the primary (VAS) and all secondary outcomes at weeks 2 and 4. This term was also used to assess group differences in VAS and RMDQ scores at both the 1- and 3-month follow-ups. Additionally, a supportive analysis compared clinical response rates at week 4 using a chi-square test or logistic regression.

A sensitivity analysis will be repeated the primary analysis on the per-protocol (PPS) set. The LMMs inherently handles missing data; multiple imputation was used for other analyses where necessary. Exploratory correlations between outcome changes will be assessed using Pearson correlation for normally distributed variables and Spearman correlation for non-normally distributed or ordinal variables.

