### Eligibility criteria

2.2

Participants will be recruited from the Rehabilitation Medicine Center/Tuina Department of Hubei Provincial Hospital of Traditional Chinese Medicine through outpatient screening and recruitment advertisements. A consecutive sampling strategy will be used: all potentially eligible sedentary individuals with chronic non-specific low back pain who attend the center during the recruitment period will be screened according to the eligibility criteria until the target sample size is reached. Sedentary behavior will be assessed using the sitting-time item of the International Physical Activity Questionnaire-Short Form (IPAQ-SF).

Participants will be eligible if they meet all of the following criteria:

(1)Aged 20–60 years;(2)Diagnosed with chronic non-specific low back pain, defined as pain localized between the lower costal margin and the inferior gluteal folds lasting for more than 12 weeks, without identifiable specific pathology;(3)Sedentary time of ≥6 h/day during a typical day;(4)Baseline VAS pain score ≥ 3 on a 0–10 scale;(5)No systematic physical therapy, manual therapy, acupuncture, or structured core muscle training within the previous 4 weeks;(6)Able to understand the study procedures, provide written informed consent, and comply with the intervention and follow-up schedule.

Participants will be excluded if they have:

(1)Red-flag conditions, including suspected fracture, infection, tumor, unexplained weight loss, fever, or history of malignancy;(2)Predominant radicular pain, progressive neurological deficit, or cauda equina syndrome;(3)Spinal surgery or major spinal trauma within the past 3 months;(4)Systemic inflammatory, rheumatic, neurological, or severe cardiopulmonary diseases;(5)Severe osteoporosis, coagulation disorders, skin infection or open wounds in the treatment area, or other contraindications to manual therapy;(6)Conditions preventing safe exercise participation;(7)Pregnancy or lactation;(8)Professional athlete status;(9)Participation in another clinical trial.

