### Outcome measurement

2.5

All outcome measures will be assessed at baseline, the end of week 2, and the end of week 4. Additionally, pain intensity and disability were re-assessed at the 1-month and 3-month follow-ups.

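### As worded, the mixed model implies one variance and one correlation across unequally spaced visits; standard errors can be wrong, mainly too small at follow-up and for the three-visit outcomes

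*Protocol article*

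**What the plan says.** The model is given in the protocol article, section 2.9 (Statistical analysis): "The model will include group, time, and their interaction as fixed effects, with participants as a random effect". The same sentence adds an adjustment for baseline. The tests come from the interaction. For weeks 2 and 4: "The group-by-time interaction term will be used to test for between-group differences in the change from baseline". For the later visits: "This term was also used to assess group differences in VAS and RMDQ scores at both the 1- and 3-month follow-ups".

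The visit schedule is in section 2.5: "All outcome measures will be assessed at baseline, the end of week 2, and the end of week 4", and in addition "pain intensity and disability were re-assessed at the 1-month and 3-month follow-ups". Table 1 labels the two follow-ups Month 2 and Month 4. VAS and RMDQ therefore have five assessments. FABQ, MyotonPRO, the isokinetic measures and PPT have three, ending at week 4.

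The safeguard in section 2.9 is residual and Q-Q plots, followed by: "If substantial violations are identified, appropriate transformations or robust sensitivity analyses will be considered".

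**The concern.** A participant random effect with no slope and no residual structure is, on its natural reading, a random intercept with independent residuals. That is compound symmetry: one variance at every visit, and the same correlation for visits 2 weeks apart as for baseline and month 4.

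Three features of the design make this doubtful:
- The gaps between visits run from 2 weeks to about 2 months.
- Treatment ends at week 4 (section 2.4), so the last two visits fall in a different phase.
- Entry requires a baseline VAS of at least 3 (section 2.2, inclusion criterion 4), which may make the baseline spread smaller than later spreads.

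If the true covariance differs, the model applies one averaged variance to every contrast. Contrasts between weakly correlated visits then get standard errors that are too small, and contrasts between strongly correlated visits get ones that are too large. At stake are the follow-up claims on VAS and RMDQ, the week-4 claims on the three-visit outcomes and, in a direction not known in advance, the primary contrast. Section 2.9 also relies on the mixed model to handle missing data, with 15% dropout allowed for. Likelihood inference under missing at random depends on a correct covariance, so the estimates are exposed as well.

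**Working it through.** **The plan's own figure.** Section 2.8 gives a difference of 1.5, SD 2.3, two-sided α 0.05 and power 80%. By normal approximation, n per arm = 2 × (1.960 + 0.842)² × (2.3/1.5)² = 36.9, so 37 per arm and 74 in total. Then 37/0.85 = 43.5, so 44 per arm and 88 in total. Both stated totals reproduce. They rest on a single-visit comparison and do not involve the covariance structure.

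**Method.** Complete data and a large sample. A random-intercept fit estimates the mean variance v and the mean covariance c over visits. Let R be the model-based SE divided by the true SE; type I error is 2Φ(−1.96R).
- Baseline as a response row: R² = 2(v − c) / Var(Y_k − Y_0).
- Baseline as a covariate with common slope b: R² = mean post-baseline residual variance / residual variance at visit k. With unit SDs, the residual variance is 1 − 2b·r_k + b², where r_k is the correlation of visit k with baseline and b is the mean of the r_k.

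The article does not settle which reading applies, so both are shown.

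**Assumed patterns for five visits, equal SDs.**
- Visit order: correlation ρ to the power of the number of visits apart.
- Stepped: baseline correlations 0.50, 0.45, 0.40, 0.30; post-baseline 0.7, 0.6, 0.5 at one, two and three visits apart.
- Calendar: correlation decays per 2 weeks, with visits taken at weeks 0, 2, 4, 8 and 16.

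**Worked cases.**
- Visit order, ρ = 0.8, row: c = (4×0.8 + 3×0.64 + 2×0.512 + 0.4096)/10 = 0.655. Month 4: R = √[2(0.345)/2(1 − 0.4096)] = 0.764. Week 4: √[0.345/0.36] = 0.978.
- Stepped, row: c = (1.65 + 2.1 + 1.2 + 0.5)/10 = 0.545. Week 4: √[0.455/0.55] = 0.910.
- Calendar, 0.95, row: c = 8.288/10 = 0.829. Week 4: √[0.171/0.0975] = 1.325. Month 4: √[0.171/0.337] = 0.713.
- Visit order, ρ = 0.5, covariate: b = 0.9375/4 = 0.234. Residual variances are 0.821, 0.938, 0.996 and 1.026, mean 0.945. Month 4: √(0.945/1.026) = 0.960, type I error 6.0%.

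| Pattern | Week-4 VAS, row | Month 4, row | Week-4 VAS, covariate | Month 4, covariate |
|---|---|---|---|---|
| Compound symmetry | 1.000 (5.0%) | 1.000 (5.0%) | 1.000 (5.0%) | 1.000 (5.0%) |
| Visit order, 0.6 | 0.965 (5.9%) | 0.827 (10.5%) | 1.013 (4.7%) | 0.935 (6.7%) |
| Visit order, 0.8 | 0.978 (5.5%) | 0.764 (13.4%) | 1.048 (4.0%) | 0.868 (8.9%) |
| Stepped | 0.910 (7.5%) | 0.806 (11.4%) | 1.019 (4.6%) | 0.948 (6.3%) |
| Calendar, 0.85 | 1.234 (1.6%) | 0.762 (13.5%) | 1.146 (2.5%) | 0.795 (11.9%) |
| Calendar, 0.95 | 1.325 (0.9%) | 0.713 (16.2%) | 1.269 (1.3%) | 0.722 (15.7%) |

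Entries are R (type I error).

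**SDs that differ by visit, all correlations 0.5.** With SDs 1.5, 2.0, 2.3, 2.4, 2.5, month-4 R is 1.013 (row) and 0.923 (covariate). With 1.5, 1.8, 2.0, 2.3, 2.6 it is 0.937 and 0.844. Week-4 VAS R across both SD sets is 1.00 to 1.18.

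**Three-visit outcomes, week 4.** With equal SDs, lag-one correlation ρ and baseline as a row, the formula reduces to R² = (3 + ρ)/[3(1 + ρ)]. At ρ = 0.6, √(3.6/4.8) = 0.866 (9.0%). At ρ = 0.8, √(3.8/5.4) = 0.839 (10.0%). The limit as ρ approaches 1 is √(4/6) = 0.816. At the mild end, with baseline as a covariate and baseline correlations 0.50 and 0.45, R = √(0.774/0.798) = 0.985 (5.4%).

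**Cost of a standard error that is too large.** If a test with 80% true power has its SE overstated by 23 to 33%, power becomes Φ(2.802 − 1.96 × 1.23) = 65% down to Φ(2.802 − 1.96 × 1.33) = 58%.

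**The case against.** The strongest objection is that the premise is inferred. The sentence says neither intercept nor only, and residual covariance, degrees of freedom and convergence rules are details that an article commonly leaves to an analysis plan, which is not shown. It stands as a limit on the claim: this is the natural reading of a stated model, not proof of what will be fitted. It does not dispose of the point, because the article does state a model and a better one is available at trivial cost.

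Three further objections carry weight. No visit-specific SD or correlation is given, so every percentage comes from an assumed pattern. The phrase on adjusting for baseline suggests baseline as a covariate; complete-data contrasts at one visit then depend on the pooled residual variance rather than on correlations between visits, and most of the errors shrink. And section 2.9 offers robust analyses. But these are only to be considered, and the trigger is plots that may show unequal spread between visits but do not target within-person correlation.

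A reader might infer that the primary week-4 test is anti-conservative. The calculations do not support that: its error changes sign with the assumed pattern. Nor do they support saying that the standard errors are wrong without condition.

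**Conclusion.** The point holds in conditional form. If the model is a random intercept alone, and correlations decay or SDs differ by visit, then:
- month-4 VAS and RMDQ standard errors are roughly 4 to 29% too small under decaying correlations (type I error about 6 to 16%);
- week-4 standard errors of the three-visit outcomes are roughly 1 to 16% too small (about 5 to 10%);
- the primary week-4 VAS standard error lies between about 9% too small and 33% too large, so its direction is not established. An error on the large side would cost power in a trial sized for 80%.

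These ranges illustrate plausible patterns and are not bounds. Unequal SDs alone can leave month 4 almost correct, and combinations of decay and rising SDs could go beyond the ranges. Dropout and small-sample degrees of freedom are ignored. The main anti-conservative risk falls on secondary and follow-up claims, so this is a worthwhile correction rather than a threat to the primary result.

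**What to change.** In section 2.9, replace the participant random effect with an unstructured within-participant covariance over visits, fitted by REML with Kenward-Roger degrees of freedom. Apply it to VAS, RMDQ and the three-visit outcomes. State the fallback in advance if the model does not converge: heterogeneous Toeplitz, then a random intercept with robust standard errors. In the same sentence, say whether baseline is a response row or a covariate. If an analysis plan already names such a structure, the article only needs to be brought into line with it.

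The cost is one or two sentences. Five visits need 5 × 6/2 = 15 covariance parameters, or 4 × 5/2 = 10 if baseline is a covariate; three visits need 6, or 3 with baseline as a covariate. That is manageable with 88 participants, though the fallback may be needed. The sample size of 74, raised to 88, does not change.

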#### Primary outcome

2.5.1

The primary outcome is the change from baseline in pain intensity at week 4. Pain intensity will be assessed using the 10-cm Visual Analog Scale (VAS), with 0 indicating “no pain” and 10 indicating “the worst imaginable pain.” The VAS is widely used in low back pain research and has demonstrated acceptable reliability, validity, and responsiveness for musculoskeletal pain assessment (31). A reduction of 2 points is commonly interpreted as clinically meaningful improvement. A 2-point difference on the VAS was defined as the minimal clinically important difference (MCID) (32).

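### The primary week-4 comparison is tested with a group-by-time interaction whose meaning is not fixed; on the usual covariate reading of the baseline adjustment it does not test the week-4 effect

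*Protocol article*

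**What the plan says.** Section 2.5.1 sets a single-visit endpoint: "The primary outcome is the change from baseline in pain intensity at week 4". VAS is measured at baseline, weeks 2 and 4, and again at the 1- and 3-month follow-ups (Section 2.5).

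Section 2.9 specifies the efficacy model: "The model will include group, time, and their interaction as fixed effects, with participants as a random effect, adjusting for baseline values". It then names the test, for VAS and for every secondary outcome at weeks 2 and 4: "The group-by-time interaction term will be used to test for between-group differences in the change from baseline". The follow-up visits use the same term: "This term was also used to assess group differences in VAS and RMDQ scores at both the 1- and 3-month follow-ups".

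Three things are left open:
- whether baseline is a level of the time factor or enters only as a covariate;
- whether the term is a single coefficient at week 4 or an overall test across visits;
- which contrast carries the primary conclusion. No week-4 group contrast is named.

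Section 2.8 sizes the trial for a two-group mean difference: "The expected between-group difference in VAS was set at 1.5 points, with a pooled standard deviation of 2.3", two-sided 0.05, 80% power.

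**The concern.** Two statements in Section 2.9 pull against each other. Adjusting for baseline usually means that baseline is a covariate and the post-baseline visits are the responses. In that model the treatment effect at week 4 is the group term plus the group-by-week-4 term (with week 2 as reference). The interaction alone only measures how the group difference moves from one visit to another. Reading the interaction as a difference in change from baseline requires baseline to be one of the response visits, and then the covariate has little or nothing left to do.

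The choice matters for the main conclusion. On the first reading, a treatment that works early and keeps working would probably be declared ineffective. Such a time course is plausible here, though not established: the Introduction and Discussion argue for rapid pain relief after manual therapy, and the first post-baseline visit is not until week 2. If the term is an overall test across visits, it can also be significant when there is no effect at week 4. Because the wording permits tests with very different power, the analyst could choose among them after seeing the data, for the primary and all secondary outcomes.

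**Working it through.** **Inputs from the protocol.** Difference δ = 1.5, SD σ = 2.3, two-sided α = 0.05, power 80%, dropout 15% (Section 2.8); 1:1 allocation (Section 2.3).

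**Assumed, because the article does not give them.** SD 2.3 at every visit; equal correlation ρ of 0.3, 0.5 or 0.7 between visits (the structure that a participant random intercept implies); several time courses of the benefit.

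**Step 1: the plan's own figure.** n per arm = 2(1.96 + 0.8416)² × (2.3/1.5)² = 2 × 7.849 × 2.351 = 36.9, so 37 per arm and 74 in total. 37/0.85 = 43.5, so 44 per arm and 88 in total. Both figures are reproduced. The steps below use n = 37 per arm.

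**Step 2: three single-visit or two-visit contrasts.** Each has SE = √(2V/n):
- baseline-adjusted difference at week 4: V = σ²(1 − ρ²);
- difference in change from baseline to week 4 (baseline as a response level): V = 2σ²(1 − ρ);
- difference between the week-4 and week-2 group effects (baseline as covariate only): V = 2σ²(1 − ρ), but the target is δ(week 4) − δ(week 2), not δ(week 4).

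At ρ = 0.5, with a week-4 effect of 1.5:
- adjusted week-4 contrast: V = 3.97, SE = 0.463, 1.5/0.463 = 3.24, power 89%;
- change from baseline: V = 5.29, SE = 0.535, 1.5/0.535 = 2.81, power 79%;
- week 4 minus week 2, constant benefit: target 1.5 − 1.5 = 0, so the rejection rate is α = 5% whatever σ, ρ or n.

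**Step 3: interaction as a joint test over k visits.** Noncentral F with λ = (n/2) × Σ(δⱼ − mean δ)² / [σ²(1 − ρ)].

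Baseline as covariate only, four post-baseline visits, ρ = 0.5, so σ²(1 − ρ) = 2.645:
- constant 1.5: sum = 0, λ = 0, power 5%;
- 0.75 at week 2, then 1.5: sum = 0.75² × 3/4 = 0.422, λ = 18.5 × 0.422/2.645 = 2.95, power 27%;
- none at week 2, then 1.5: sum = 1.5² × 3/4 = 1.688, λ = 11.8, power 83%.

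**Step 4: results over the assumed range.**

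| Test and true benefit | ρ = 0.3 | ρ = 0.5 | ρ = 0.7 |
|---|---|---|---|
| Baseline-adjusted week-4 contrast, 1.5 at week 4 | 83% | 89% | 97% |
| Covariate only, interaction: constant 1.5 | 5% | 5% | 5% |
| Covariate only, interaction: 0.75 at week 2, then 1.5 | 20% | 27% | 43% |
| Covariate only, interaction: none at week 2, then 1.5 | 67% | 83% | 97% |
| Baseline a response level, week-4 coefficient: 1.5 at week 4 | 65% | 79% | 95% |
| Baseline a response level, joint test: constant 1.5 | 66% | 82% | 97% |

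Simulation at ρ = 0.5 (10,000 runs) agrees: constant benefit 5.3% for the covariate-only interaction, 88-89% for the adjusted week-4 contrast and about 79% for the change comparison.

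**Step 5: the joint test with no week-4 effect.** Take a benefit of 1.5 at week 2 only. With baseline as covariate the sum is again 1.688, so the overall interaction rejects about 83% of the time at ρ = 0.5. With baseline as a response level the sum is 1.5² × 4/5 = 1.8 and λ = 12.6, giving about 82%. A separate simulation (4,000 runs) gave 82% and 81%, against 5% for the week-4 contrast.

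**Step 6: the covariate when baseline is also a response.** A baseline covariate that is constant over time shifts all of a participant's rows alike and cancels from the within-participant contrast. In model fits on complete data, the week-4 interaction coefficient equalled the raw difference in mean change to within 1e-13.

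**The case against.** The strongest reply is that Section 2.9 says what the term is for: differences in change from baseline, at named visits. An interaction expresses that only if baseline is a level of time, and the week-4 coefficient is then exactly the endpoint of Section 2.5.1. This stands. A reader might infer that the planned test is simply not the week-4 effect, or that the trial has 5% power. The document does not support either as a flat statement; both depend on the covariate-only reading, and the 5% also on a benefit that is complete by week 2.

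A reader might also infer that the test is a joint one on any reading, or that the sample size was computed for a different test. Neither is supported. Visits are named, so a visit-specific coefficient is a fair reading. With baseline as a response level the test is a difference in mean change, which fits Section 2.8: at ρ = 0.5 the SD of change is 2.3 × √(2 × 0.5) = 2.3.

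It is also fair that the covariate is exactly inert only with complete data. With about 15% dropout, one check gave slightly different estimates with and without it (-1.571 against -1.507; SE 0.465 against 0.454). The adjustment gained is small.

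Finally, model detail may be left to an analysis plan that is not shown. That excuses missing detail. It does not cover this point, because the article itself names the interaction as the test and pairs it with "with participants as a random effect, adjusting for baseline values", and the two fit together poorly on either reading.

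**Conclusion.** The concern holds as an ambiguity in a stated primary test, with serious consequences on one of its two readings.

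- **Baseline as covariate only:** the interaction does not test the week-4 effect. Power for a true 1.5-point benefit at week 4 runs from 5% (full by week 2 and sustained) through 20-43% (half present at week 2) to 67-97% (none at week 2), against 83-97% for the adjusted week-4 contrast.
- **Baseline also a response level:** the week-4 coefficient is a valid test of the endpoint, at 65%, 79% and 95% power for ρ of 0.3, 0.5 and 0.7. The cost is the lost baseline adjustment, which would give 83%, 89% and 97%.
- **Overall joint test on either reading:** it is not specific to week 4 and can reject when there is no week-4 effect.

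The visit SDs, correlations and time courses are assumptions; the covariate-only 5% for a constant benefit does not depend on the SD, the correlation or the sample size. The planned 74 evaluable and 88 recruited participants are reproduced and not questioned.

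**What to change.** Replace the sentence on the interaction term in Section 2.9 with a statement of this kind:

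*The primary test is the model-based between-group difference in VAS at week 4 (group plus group-by-week-4), two-sided 0.05, reported with a 95% confidence interval. The model takes the post-baseline visits as responses, with categorical visit, group, group-by-visit and baseline VAS as a covariate, preferably interacting with visit.*

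Report the week-2, 1-month and 3-month differences from the same model as secondary contrasts. Do not use the overall interaction as the primary test; it can be shown descriptively. Use the same form for the secondary outcomes, with the visits at which each is measured.

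This adjusts for baseline as Section 2.9 intends and targets the endpoint of Section 2.5.1. On the assumptions above, it is at least as powerful for a week-4 effect as the week-4 interaction coefficient on either reading. It costs a wording change in the protocol and analysis plan before unblinding, with no new participants or data.

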**Discussion:**

The central hypothesis is that the integration of manual therapy and core stability exercise produces a synergistic, non-linear effect rather than a simple additive one. Manual therapy acts as a “passive preparation” to create a time-sensitive “therapeutic window” by reducing pain and muscle hypertonicity. By immediately introducing core stability exercise within this window, the model optimizes target muscle recruitment and movement quality. This comprehensive approach aims to achieve a more efficient reversal of the pathological cycle in sedentary populations.

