### Randomization, allocation concealment, and blinding

2.3

Following baseline assessments, participants will be randomly allocated in a 1:1 ratio. An independent researcher will generate the randomization sequence using a computerized random-number generator (SAS, version 9.1.3). To ensure allocation concealment, assignments will be placed in sequentially numbered, opaque, sealed envelopes. The treating therapist will open the next available envelope in front of each participant to reveal their group assignment.

All researchers, including outcome assessors and statisticians, will remain blinded to group allocation throughout the trial. The interventionists (manual therapist and core muscle exercise instructor) were necessarily unblinded but were strictly excluded from outcome assessment and data analysis to prevent bias. Participants will be instructed not to disclose their group allocation or treatment details to the outcome assessors during any assessment or follow-up visit.

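### The exploratory correlations between outcome changes name no adjustment for arm or baseline; if run across both arms, they can show associations that do not exist within arms

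*Protocol article*

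**What the plan says.** The last paragraph of section 2.9 gives the whole specification: "Exploratory correlations between outcome changes will be assessed using Pearson correlation for normally distributed variables", and "Spearman correlation for non-normally distributed or ordinal variables". That fixes the variables (changes in outcomes) and the type of coefficient. It does not say whether the arms are pooled, taken separately or adjusted for, and it names no baseline term, no pairs of outcomes and no interpretation.

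The efficacy model in the same section is more explicit: "The model will include group, time, and their interaction as fixed effects, with participants as a random effect, adjusting for baseline values".

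The abstract's Discussion says that manual therapy opens its therapeutic window "by reducing pain and muscle hypertonicity". Section 2.9 does not link the correlations to that statement; it calls them exploratory.

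**The concern.** Read plainly, the sentence describes a simple correlation of raw change scores across participants. In a two-arm trial such a coefficient has two components that say nothing about whether outcomes move together within participants given the same treatment.

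- **Arm.** If treatment moves both outcomes, the difference in arm means alone makes them correlate in the pooled sample. This component grows as the treatment works better.
- **Baseline.** A raw change contains the baseline value with a minus sign. If two outcomes are correlated at baseline, their changes inherit part of that correlation even when nothing links their later course.

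Choosing between Pearson and Spearman removes neither. What is at stake is interpretation: a reader who has met the article's account of how the treatment works could take a correlation between, say, change in stiffness and change in pain as support for it. That pair is an illustration; the plan names none. The ten measures in section 2.5 (VAS, RMDQ, two FABQ subscales, frequency, stiffness, peak torque, total work, endurance index, PPT) allow 10 × 9 / 2 = 45 pairs.

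**Working it through.** **Inputs from the protocol article**

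- Section 2.8: "The expected between-group difference in VAS was set at 1.5 points, with a pooled standard deviation of 2.3", so d = 1.5 / 2.3 = 0.65; "the type I error probability (α) for a two-tailed test was set at 0.05"; "the statistical power (1−β) at 80"%.
- Section 2.3: "participants will be randomly allocated in a 1:1 ratio".
- Section 2.8: 74 participants before dropout, 88 recruited.

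**The plan's own figure.** n per arm = 2 × (1.960 + 0.842)² × 2.3² / 1.5² = 36.9, rounded up to 37, so 74 in total. With 15% dropout, 37 / 0.85 = 43.5, rounded up to 44 per arm, so 88. Both figures are reproduced. The plan states no figure for the correlations.

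**Arm component.** Assume zero correlation within arms, 1:1 allocation, unit within-arm SD, and standardised effects d₁ and d₂ scored in the direction of improvement. The pooled correlation is then

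r = (d₁d₂/4) / √[(1 + d₁²/4)(1 + d₂²/4)].

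For d₁ = d₂ = 0.65: 0.1056 / 1.1056 = 0.096. For 0.65 and 1.0: 0.1625 / √(1.1056 × 1.25) = 0.138.

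The effect on the second outcome is an assumption throughout. The rates below come from 40,000 simulated trials per row, with a two-sided Pearson test at 0.05.

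| d for VAS | d for second outcome | pooled r | p < 0.05, N = 74 | p < 0.05, N = 88 | arm-adjusted, N = 74 |
|---|---|---|---|---|---|
| 0.65 | 0.2 | 0.03 | 5.6% | 6.1% | 5.0% |
| 0.65 | 0.5 | 0.075 | 9.7% | 10.3% | 5.0% |
| 0.65 | 0.65 | 0.096 | 12.7% | 14.0% | 4.8% |
| 0.65 | 1.0 | 0.14 | 22.2% | 24.9% | 5.0% |

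The smallest |r| that reaches p < 0.05 is 0.23 at N = 74 and 0.21 at N = 88.

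**Baseline component.** Assume no treatment effect, correlation r_b between the two outcomes at baseline, correlation ρ between baseline and follow-up for each, and independent follow-up errors. The covariance of the changes is (1 − ρ)² r_b and each variance is 2(1 − ρ), so

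r = r_b (1 − ρ) / 2.

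Both r_b and ρ are assumed; neither is in the article. N = 74, 10,000 simulated trials per cell.

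| r_b | ρ = 0.3 | ρ = 0.5 | ρ = 0.7 |
|---|---|---|---|
| 0 | r = 0; 4.6% | r = 0; 5.3% | r = 0; 5.1% |
| 0.3 | r = 0.105; 14.4% | r = 0.075; 10.0% | r = 0.045; 6.4% |
| 0.5 | r = 0.175; 32.4% | r = 0.125; 18.5% | r = 0.075; 9.7% |

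The entry criterion of VAS ≥ 3 truncates one baseline. With an assumed cut at 1 SD below the mean, the rates for r_b of 0.3 to 0.5 fall to between 5.9% and 17.0%.

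Under this model, once both baselines are conditioned on, only the independent follow-up errors remain, so the partial correlation is zero. For Pearson, adjusting changes for both baselines gives the same partial correlation as adjusting the week-4 values for them, because the two differ only by variables already adjusted for.

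**The case against.** The strongest reply is that the sentence is a one-line summary of exploratory work in a condensed article. It does not say that the arms are pooled, and an analysis plan that is not shown may specify within-arm or partial correlations. That stands as far as pooling goes: a reader might infer that pooling is planned, but the document does not state it, so the arm component is conditional on it. It does not remove the point. The sentence does fix change scores and a simple coefficient, next to a model that names group and baseline, and separate analysis by arm would leave the baseline component in place.

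It can also be said that a pooled coefficient correctly describes the trial sample, and that the excess over 5% is an error only if a within-arm association is the target. That is fair. The problem lies in how the number would be read, and the plan commits to no reading.

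Three stronger readings are tempting and are not supported:

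- A reader might infer that regression to the mean can link any two outcomes. It cannot: with no baseline correlation, r is 0 and the rate stays near 5%. Baseline correlation is plausible here, since the Introduction itself describes psychological distress as associated with poorer muscle endurance and function, but its size is not given.
- A reader might infer that these correlations are the only test of the proposed mechanism. Section 2.9 calls them exploratory, and the mixed models compare the arms on all secondary outcomes, including stiffness and PPT, with group and baseline in the model. The limitations paragraph also asks for caution with the biomechanical outcomes.
- A reader might infer that a working treatment would routinely yield spurious support. At d = 0.65 on both outcomes, r is about 0.10, well below the critical 0.23, and about 87% of pairs stay non-significant. Effects of 1.0 on both would give r = 0.20 and 41%, but nothing in the article supports 1.0 for VAS.

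**Conclusion.** The concern holds in a limited form. As written, the correlations carry no stated protection against a between-arm component or against shared baseline variation. If arms are pooled, nominal significance without any within-arm link rises from 5% to about 6% to 22% per pair at N = 74. This uses the plan's d = 0.65 for VAS and an assumed 0.2 to 1.0 for the second outcome. For outcomes correlated at baseline, unadjusted changes give about 6% to 32% for an assumed baseline correlation of 0.3 to 0.5 and an assumed baseline-to-follow-up correlation of 0.7 down to 0.3, and less after selection on the baseline value. The two components were computed separately, not combined. No primary result, sample size or stated decision depends on this sentence, so it is a minor improvement.

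**What to change.** Amend the sentence in section 2.9 to specify partial correlations, Pearson or rank-based as the distributions require, adjusted for arm and for the baseline values of both outcomes. Report each r with its 95% CI, and describe it as exploratory within-arm association, not evidence of mediation.

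The cost is one sentence, trivial programming and three degrees of freedom per correlation (arm and two baselines). All the data are already collected. The downside is that some correlations will be smaller than their unadjusted versions.
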